### Data monitoring

Monitoring will be done at least twice in each study center (shortly after the inclusion of the first patient and at the end of the study) by personal visits from a clinical monitor of the Coordination Centre for Clinical Trials (KKS), Ruprecht-Karls-University, Heidelberg. The monitor will check patients´ informed consent and review the entries in the eCRFs on the basis of source documents. The investigator must allow the monitor to verify all essential documents and must provide support at all times. By frequent communication (letters, telephone, or email), the site monitor will ensure that the trial is conducted according to the protocol and regulatory requirements.

### Harms

Adverse events (AE) are restricted to complications of study-related blood draws (local lesions at puncture site or volume of blood draws). Such minor AEs are recorded in the eCRF. Serious AEs (SAE) resulting in death, a life-threatening state, a prolongation of existing hospitalization, a persistent or significant disability or incapacity due to study participation are not expected. This is due to the fact that standard-of-care diagnostics and treatment are guaranteed in both study groups, with the only difference that additional information resulting from NGS-based digital precision diagnostics are made available in IG patients.

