#### Facultative expert consultations

In terms of an anti-infective stewardship, facultative expert consultations are available for patients in both study groups. However, they are particularly recommended for patients of the IG group (where results of NGS-based diagnostics are made available to the commissioning physician), if NGS-based digital precision diagnostics and standard-of-care microbiological analyses are contradictory. The characteristics and results of consultations in both groups will be monitored and described in detail in the final publication. Because the involvement of the expert group is possible for all patients, their final effect on patient’s outcome is expected to be comparable between both study groups.

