### Sample size calculation

For sample size calculation, a sophisticated secondary outcome analysis of the following four large sepsis studies of the SepNet Study Group (VISEP [15], MAXSEP [16], HYPRESS [17], and SISPCT [18]) was performed, in which the above described OCO-groups were represented as follows: OCO 1: 33%, OCO 2: 3%, OCO 3: 22%, OCO 4: 14%, and OCO 5: 28%. It is assumed that the anti-infective treatment period in OCO 1 and OCO 2 is 7 days in average, whereas it is prolonged up to 15 days (with a standard deviation of 10 days) in average in OCO 3 and OCO 4. Based on the assumption that the OCO group can be improved by at least 2 stages in 42% of IG patients in parallel to a shortening of the anti-infective treatment by 2 days, this would result in a power of 90% with 180 patients in each of the two study groups (CG, IG), provided that an IG patient has a lower DOOR/RADAR score as compared to a CG patient with a relative effect of *p* = 0.6. Including an additional drop-out rate of 12.5% (and considering these patients as OCO 5) would finally result in an overall sample size of 410 patients (CG: *n* = 205/IG: *n* = 205).

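### The Harms section expects no serious events because added NGS information is the only difference between arms, yet the trial relies on that information changing treatment, and relapse, treatment restart and resistance are not identified as such.

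*Protocol article*

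**What the plan says.** All references are to the protocol article.

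**Harms.** "Adverse events (AE) are restricted to complications of study-related blood draws", meaning local lesions or the volume drawn. After listing the usual criteria for serious events, the section says that these, ending with "a persistent or significant disability or incapacity due to study participation are not expected". The reason given is that "standard-of-care diagnostics and treatment are guaranteed in both study groups". The section adds that the arms differ in nothing but the extra NGS results supplied to the intervention arm.

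**How NGS is meant to work.**
- *Data analysis and result communication* sends the NGS result to the commissioning physician.
- *Primary outcomes* contrasts intervention patients with controls whose anti-infective treatment follows standard microbiology alone.
- *Sample size calculation* assumes an OCO gain of at least two stages in 42% of intervention patients, "in parallel to a shortening of the anti-infective treatment by 2 days".
- *Justification for enrolment of participants not capable of giving consent* expects outcome to improve through earlier optimisation of the anti-infective regimen.
- *Facultative expert consultations* particularly recommends a consultation in the intervention arm "if NGS-based digital precision diagnostics and standard-of-care microbiological analyses are contradictory".

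**What is measured.** The primary score combines 28-day survival, ICU/IMC stay, AKI needing RRT and days of anti-infective treatment. Table 2 adds, among others, later mortality, ventilation, time to shock resolution, ongoing RRT, hospital stay, cumulative anti-infective need and start of targeted treatment.

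**The concern.** A diagnostic result that can shorten treatment and improve outcome can also mislead. The plausible harm of this intervention is a treatment change made on a wrong or incomplete result, not a puncture-site lesion. The adverse-event definition covers only the latter, and the reasoning for expecting no serious events passes over the treatment change on which the trial depends.

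The primary score counts fewer treatment days as better within an OCO category. A reader of the results will ask whether shorter treatment came with more relapse, more restarts or a different pattern of resistance. The Abstract presents the trial as a basis for making NGS part of the national standard, and the Background itself names selection of multi-drug resistant pathogens and antibiotic toxicity as harms in this setting. With the outcomes listed, that question can be answered only indirectly.

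**Working it through.** **1. The two lines of reasoning side by side.** Harms: standard care for all; information is the only difference; hence no serious events due to participation are expected. Primary outcomes, Sample size calculation and the justification for enrolling patients unable to consent: the information changes the regimen, shortens it by 2 days and improves outcome. Both can be true as descriptions, but the inference in Harms does not follow once the information is expected to alter treatment.

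**2. Which harms the listed outcomes would show.**

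| Possible harm | Where it would appear |
|---|---|
| Death | OCO 5; 90- and 180-day mortality |
| AKI needing RRT | OCO 2 and 4; ongoing RRT |
| Prolonged illness | ICU/IMC stay, hospital stay, ventilation, shock resolution |
| Relapse that is re-treated | Extra anti-infective days or longer stay, not labelled as relapse |
| New infection, treatment restart | As above, not labelled |
| Resistant organisms, *C. difficile* | No dedicated outcome |
| Drug toxicity short of RRT | No dedicated outcome |

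**3. What the score does with a relapse.** For OCO 1 to 4 the score is OCO + d/(M + 1), where d is days treated and M the maximum number of days. The article gives no value for M, so it stays symbolic.
- Patient A has an uneventful course of 7 days (the average assumed for OCO 1 and 2): 1 + 7/(M + 1).
- Patient B stops 4 days early, at day 3, relapses and is re-treated for 4 days: d = 3 + 4 = 7, so again 1 + 7/(M + 1).

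If both remain in OCO 1, the scores are identical. The relapse did cost B 4 days, but the score cannot show why.

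**4. What the score cannot do.** Since d ≤ M, the fraction is below 1. Short treatment cannot lift a patient above someone in a better OCO category, and death scores a flat 5.

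**5. How much shortening alone could contribute.** The planned relative effect of 0.6 agrees with the stated sample size under the Noether formula (two-sided 0.05 assumed): (1.960 + 1.282)² / (12 × 0.25 × 0.1²) = 350.2 in total, or 176 per arm against 180 stated; power at 180 per arm is 90.8%. This only confirms 0.6 as the design value and says nothing about harms.

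Suppose both arms have the planned OCO shares, so that only treatment days differ. Treatment days decide a pair only when both patients are in the same category from 1 to 4:

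0.33² + 0.03² + 0.22² + 0.14² = 0.1089 + 0.0009 + 0.0484 + 0.0196 = 0.1778.

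- Upper bound, if the intervention patient has fewer days in every such pair: 0.5 + 0.1778/2 = 0.589.
- With a 2-day shift, normal day counts and an SD of 10 days in every category (the article attaches this SD to OCO 3 and 4): Φ(2/(10√2)) = Φ(0.141) = 0.556, giving 0.5 + 0.1778 × 0.056 = 0.510.

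**The case against.** The best defence is that Harms promises a floor of standard care and does not deny that treatment may differ. A reader might infer that the section claims identical treatment in both arms; it does not. Its reason also attaches to the statement on serious events, while the blood-draw restriction merely stands beside it. Both points are right and limit the criticism to the inference drawn from the only difference.

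A reader might also infer that under-treatment goes unmeasured, or that relapse would leave no trace. The documents do not support this. Death, RRT-dependent AKI, stay, ventilation and shock resolution are compared by arm. Re-treatment by day 28 raises the treatment-day count in the primary score and in the cumulative-need outcome. RRT-dependent AKI is also the toxicity that the Background singles out. Nor can the trial readily succeed by shortening treatment alone, as steps 4 and 5 show.

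The consultation text is conditional and describes a safeguard, consultations are to be monitored and reported, and intervention patients keep full standard microbiology. These features reduce the risk but do not measure it.

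Finally, tabulation of recorded data is commonly left to the SAP. That does not remove the point: the adverse-event restriction and its justification are stated in the article itself.

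**Conclusion.** The point holds as a matter of consistency, with a limited gap in measurement. The reasoning in Harms must be reconciled with the sections that make changed and shorter treatment the mechanism of benefit. Severe harm is largely visible by arm. Not identified as such are new or recurrent infection, restart of anti-infective treatment, and resistant organisms.

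The documents give no rate for these events, so no number of affected patients can be stated. The primary analysis and the sample size are untouched. The figure of about 0.51 rests on equal OCO shares in both arms, normal day counts and a common SD of 10 days; the bound of 0.589 needs only the equal shares. This is a change that should be made, because without it the trial cannot say directly whether shorter treatment came with more relapse or resistance.

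**What to change.** 1. Reword Harms so that it no longer infers the absence of treatment-related harm from NGS information being the only difference. State that the information may change anti-infective treatment and that the consequences are followed by arm.
2. Keep the blood-draw adverse events as they are.
3. Add a short predefined safety list, reported descriptively by arm to day 28:
   - anti-infective treatment restarted after it was stopped, derived from the start and stop dates already collected, provided that they are kept per course;
   - new or recurrent infection;
   - resistant organisms or *C. difficile* in routine microbiology.

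**Cost.** A few eCRF items, no added procedures, and no change to the primary test or sample size. New or recurrent infection probably needs its own item. At present, routine findings from specimens other than blood enter the evaluation only within 3 days of NGS sampling, so the microbiology item needs its own window to day 28, the same in both arms.

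**Downside.** Routine microbiology depends on local testing practice, and in an open-label trial the intensity of testing may differ by arm. The results should be read descriptively.

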### Ethics

Described procedures are meant to ensure that all parties involved abide by the principles of Good Clinical Practice (GCP) [19, 21] and those stipulated in the Declaration of Helsinki [22]. The study will be conducted in accordance with local statutory and implementing provisions.

### Research ethics approval

Prior to the beginning of the clinical trial, the study protocol, the patient information and informed consent, and all other required documents will be submitted to the competent ethical review committees of all participating centers. A first positive ethical vote has been given by the Ethics Committee of the Medical Faculty of the University Duisburg-Essen (Trial Code No. 20-9352-BO).

### Consent or assent

The members of the study group must inform eligible patients, both orally and in writing in an intelligible form about nature, significance, and implications of the study. Before participants can be enrolled in *DigiSep*, they must consent to participation in writing. For potential trial participants who are incapable, the following procedure applies: If a legal guardian exists, they are duly informed in accordance with the regulations and subsequently consent to participation in writing. If no legal guardian exists, participants are enrolled in the clinical trial after a near family member has been informed about nature, significance, and implications of the trial and has agreed to participation in the study mindful of the interest of the patient concerned (also by telephone). In summary proceedings, the designation of a legal guardian is begun at the district court. If no near family member is available, participants are enrolled after a guardianship judge or an independent medical consultant has been informed about nature, significance, and implications and has agreed to participation in the study mindful of the interest of the patient concerned (also by telephone). A near family member is appointed legal guardian earliest possible; they are duly informed in accordance with the regulations and subsequently consent to participation in writing (delayed consent). In any case, informed consent of study participants is sought retrospectively once they are capable of giving consent again.

### Justification for enrolment of participants not capable of giving consent

Bloodstream infections remain one of the major challenges in intensive care medicine, leading to sepsis or even septic shock in many cases. Due to the lack of timely diagnostic approaches with satisfying performance characteristics, mortality rates of sepsis are still unacceptably high. However, a prompt diagnosis of the causative microorganism is critical to improve outcome of bloodstream infections. Although various targeted molecular tests for blood samples are available, time-consuming blood culture-based approaches represent the international gold standard for identifying the underlying pathogen. With regard to these alarming figures, the presented clinical trial (*DigiSep*) is designed to investigate a comprehensive diagnostic approach, including NGS-based digital precision diagnostics, standard-of-care microbiological analyses, and facultative expert discussions. The majority of affected patients are sedated and given artificial ventilation. Even before being sedated, affected patients may be incapable of giving consent due to the underlying severe infection, inflammatory response, and severe pain. Therefore, in these cases, informed consent to participate in *DigiSep* needs to be given by a legal guardian until the affected patient is capable of consent. Nevertheless, especially these critically ill patients need to be enrolled in *DigiSep*, in order to assess the diagnostic value of the above described holistic and comprehensive approach for early detection of the causative microorganism in sepsis. This might help to improve outcome of patients suffering from sepsis due to an early optimization of the anti-infective treatment regime. This might especially be true for patients where classic microbiological or molecular diagnostic approaches fail.

### Confidentiality

Data collected are handled in accordance with the provisions of the Federal Data Protection Act (BDSG) [23]. During the clinical trial, participants are solely identified by a distinct reference number. For storage on a computer, the provisions of the BDSG [23] are abided by. Data are handled with strict confidentiality. For protection of these data, organizational measures are taken to prevent disclosure to unauthorized third parties. The relevant rules of the country-specific data legislation are complied with.

### Protocol amendments

Changes to the protocol are made in writing and require the approval of all signatories of the protocol. Subsequent amendments also require a positive assessment from the competent ethics committee.

### Dissemination

The *DigiSep* trial is planned to be reported in scientific peer-reviewed journals. The results will also be presented at relevant scientific conferences and symposiums. All contributors to the study will be offered authorship if they fulfill the International Committee of Medical Journal Editors (ICMJE) recommendations for authorship. No professional writers will be used.

## Discussion

Despite an underlying infection, positive blood cultures revealing the causative pathogen can only be obtained in a minority of septic patients [16, 24, 25]. This is at least partially attributable to technical shortfalls of blood culture processing. Moreover, the presence of strictly localized foci, fastidious organisms or very low rates of viable microorganisms in blood stream increase the risk of false-negative blood culture results [26]. Due to this diagnostic dilemma, culture-independent molecular diagnostic procedures, such as polymerase chain reaction (PCR)-based techniques, have been developed for identifying the causative pathogen in infected patients [27–31]. However, due to technical limitations of these PCR-based approaches (e.g., inability to quantify patients´ bacterial load in blood stream, restricted detection of antibiotic resistance markers, restricted pathogen detection depending on the included primers (= targeted approach), increased occurrence of contradictory or ambiguous results, low positive predictive value), this technique also appears to be far from perfect and has therefore not been widely applied in daily clinical routine [7]. A new molecular diagnostic concept of unbiased sequence analyses of circulating cell-free deoxyribonucleic acid (cfDNA) in human plasma samples by NGS revealed promising results and might therefore be a suitable diagnostic tool for critically ill patients suffering from bloodstream infections [9, 11]. As compared to PCR-based assays, NGS allows for a data-driven diagnosis without the need for specific primers (= open approach) and has the potential to detect bacterial, fungal and viral pathogens as well as parasites in one single assay. Moreover, by establishing a proprietary statistical framework, this new NGS-based approach enables a reliable differentiation between the disease-causing pathogen and potential microbial contaminants (e.g., coagulase-negative staphylococci). This goes far beyond state-of-the-art molecular approaches for the diagnosis of infecting organisms in septic specimens and might be especially useful for the diagnosis of cases where classic microbiological or molecular diagnostic approaches fail.

A potential limitation of the present study may be the design as an open-label trial without blinding. Blinding of the treating physicians, which in part belong to the data collectors, is not possible because they may have to interact with the anti-infective expert group whenever necessary. Moreover, the statisticians will not be blinded because they analyze data regarding group outcome. With respect to their group allocation patients may not be informed initially, but systematic blinding is not part of the protocol.

## Trial status

Protocol version: Version 2 (July 14, 2020)

Patient and data recruitment will be started as soon as the positive votes of all involved local ethic committees have been received. Recruitment is expected to be completed by June 2023.

## Data Availability

The datasets generated and/or analyzed during the current study are available from the corresponding author on reasonable request.

## Abbreviations

AE: Adverse events
AKI: Acute kidney injury
BDSG: Federal data protection act
BGB: German civil code
BSI: Blood stream infection
cfDNA: Cell-free deoxyribonucleic acid
CG: Control group
eCRF: Electronic case report forms
DNA: Deoxyribonucleic acid
DOOR: Desirability of outcome ranking
DRKS: German clinical trials register
GCP: Good clinical practice
ICD: International classification of diseases
ICU: Intensive care unit
IG: Intervention group
IMBI: Institute for medical biometry and informatics
IMC: Intermediate care unit
ITT: Intention to treat
KKS: Coordination centre for clinical trials
LOS: Length of stay
MAP: Mean arterial pressure
NGS: Next-generation sequencing
OCO: Overall clinical outcome
PCR: Polymerase chain reaction
PCT: Procalcitonin
QoL: Quality of life
RADAR: Response adjusted for duration of antibiotic risk
RRT: Renal replacement therapy
SAE: Serious adverse event
SAP: Statistical analytic plan
SGB: Social security statute book
SOFA: Sequential organ failure assessment
SOP: Standard operation procedure
TIFOnet: Translational intensive care research network on organ dysfunction
